### Procedures

The SPIRIT flow diagram detailing study procedures can be found in Fig. 1. Once a patient provides written consent and is deemed eligible to be enrolled in the study, they will be assigned a patient identification number and randomized to either the FIRE or SOC group. A randomization schedule will be prepared by an investigator ([name]) not involved in data collection or intervention delivery using statistical software (SAS v9.4 PROC PLAN). Within each site, 50 patients will be randomly assigned to one of two groups (FIRE or SOC group). To ensure balance in groups over time, randomization will be completed in sequential sets of 10 subjects (5 FIRE and 5 SOC) within each site. Randomization plans include an additional 30 subjects to account for anticipated attrition during the study. Once completed, the randomization plan will be provided to the study coordinator at each site. The investigators will be blinded to group allocation by concealing assignments in sealed opaque envelopes. The treating rehabilitation specialist will retrieve the group assignment from the envelope following collection of baseline data.

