### Power analysis

The primary comparisons for all aims are the comparisons between FIRE and SOC groups at 6 months for the CAIT (Aim 1), posteromedial reach direction of the SEBT (Aim 2), and the Foot and Ankle Ability Measure Sport (Aim 3). A two-sample t-test comparing the change score between the FIRE and SOC groups will have at least 95% power to detect an effect size of 0.6 between the group means when the sample size is 150 (75 per group), assuming a two-sided significance level of 0.05. In the case that attrition reaches 40%, the sample size will still allow for 80% power to detect the same effect.

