### Statistical plan and data analysis

Continuous variables will be summarized with descriptive statistics and categorical variables will be summarized with counts and percentages. Change scores and percent change scores will be calculated from baseline for follow-ups at post-intervention, 6-, 12-, and 24-months; the primary outcome for all aims is the 6-month change score. Simple comparisons between groups will be performed using two-sample t-tests for continuous variables and chi-square tests of independence for categorical variables. Effect sizes will be interpreted as weak (≤ 0.39), moderate (0.40–0.69), or strong (≥ 0.70). A two-sided significance level of 0.05 will be used for all statistical tests. All analyses will be completed with SAS v9.4 (SAS Institute, Cary, NC, USA).

Although groups will be randomly assigned, potential covariates will be examined with bivariate analyses, and comparisons requiring covariate adjustment will use regression modeling (e.g. ANCOVA, logistic regression); unadjusted and adjusted estimates will be presented with 95% confidence intervals. Potential covariates include: baseline outcome values, demographic variables (e.g., sex, age, height, weight, data collection site), prognostic indicators (e.g., number of previous ankle sprains, frequency of episodes of giving way, Identification of Functional Ankle Instability score), and intervention compliance (% sessions completed).

To examine the trajectory over time and whether the groups change differently over time, mixed model approaches may be used. Comparisons between groups, time points, and the interaction of group and time will be made using linear mixed models or generalized linear mixed models, as appropriate. Mixed model analyses allow for a repeated measures approach with flexibility in variance–covariance structure while also providing estimates in the presence of potential covariates. Unadjusted and adjusted estimates will be provided by condition and time; significant group-time interactions will allow for presentation of results by condition for each time point. While the primary analyses across all aims will be the comparison of group means, the analyses for Aim 1 will additionally include the estimation of recurrent ankle sprain rates at 6, 12, and 24-months for the FIRE and SOC conditions. Moreover, time to recurrent injury will also be examined.

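### Primary 6-month comparisons rest on an unadjusted change-score t-test, with baseline and site left as optional screened covariates: valid, but precision is given up and no leading estimate is named

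*Protocol article*

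**What the plan says.** In the protocol article, Statistical plan and data analysis states that "the primary outcome for all aims is the 6-month change score" and that "Simple comparisons between groups will be performed using two-sample t-tests for continuous variables and chi-square tests of independence for categorical variables". Power analysis sizes the trial on the same test: "A two-sample t-test comparing the change score between the FIRE and SOC groups will have at least 95% power" for an effect size of 0.6 with 75 per group, and 80% power if attrition reaches 40%. It names the 6-month comparisons as CAIT (Aim 1), SEBT posteromedial reach (Aim 2) and FAAM Sport (Aim 3).

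On adjustment, the analysis section says that "potential covariates will be examined with bivariate analyses, and comparisons requiring covariate adjustment will use regression modeling". It gives no criterion for when a comparison requires adjustment. The candidate list includes the baseline value of the outcome, data collection site, and the percentage of intervention sessions completed. Unadjusted and adjusted estimates are both to be presented with 95% confidence intervals, and the text does not say which one leads.

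Under Procedures, "randomization will be completed in sequential sets of 10 subjects (5 FIRE and 5 SOC) within each site". Site is therefore a factor of the design, known before any outcome is seen.

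**The concern.** A change score subtracts the whole baseline value, which fixes the baseline coefficient at 1. ANCOVA estimates that coefficient. Whenever the true coefficient is below 1, the change score carries extra noise. It also over-corrects for any chance baseline imbalance in the sample, although it remains unbiased over randomisations.

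Three things are at stake.

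1. **Precision.** Baseline and site are recorded for every patient, so leaving them out of the leading analysis gives up information already in hand.
2. **A settled estimate.** If the covariates are chosen after bivariate examination, the content of the adjusted model depends on the data. With no leading estimate named, a disagreement between the unadjusted and adjusted results has no agreed resolution.
3. **A post-randomisation covariate.** Compliance can itself be affected by allocation, since the two programmes differ in content. Adjusting for it in an intention-to-treat comparison can bias the treatment contrast.

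**Working it through.** **Inputs from the article:** effect size 0.6 on the change score; two-sided alpha 0.05; 75 per group; 40% attrition, so 0.6 × 75 = 45 per group; randomisation blocked within three sites.

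**Assumed, because the article does not give it:** the correlation r between baseline and 6-month values, taken over 0.3 to 0.9.

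**Step 1. The stated power.** For a two-sample t-test, the noncentrality is d × √(n/2) with 2n − 2 degrees of freedom.

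- n = 75: 0.6 × √37.5 = 3.67 on 148 df, power 95.5%. The article says at least 95%.
- n = 45: 0.6 × √22.5 = 2.85 on 88 df, power 80.4%. The article says 80%.

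Both figures reproduce.

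**Step 2. ANCOVA against the change score, equal SDs.** With unit SDs, the change score has variance 2(1 − r) and the ANCOVA residual has variance 1 − r². The ratio is (1 − r²) / [2(1 − r)] = (1 + r)/2. The same treatment difference then has effective size 0.6 / √((1 + r)/2). Degrees of freedom are 2n − 5 (intercept, group, baseline, two site terms). No variance reduction is credited to site.

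| r (assumed) | Variance ratio | SE ratio | Effective size | Power, 75 per arm | Power, 45 per arm |
|---|---|---|---|---|---|
| t-test on change | 1 | 1 | 0.600 | 95.5% | 80.4% |
| 0.3 | 0.65 | 0.806 | 0.744 | 99.5% | 93.7% |
| 0.5 | 0.75 | 0.866 | 0.693 | 98.8% | 90.1% |
| 0.7 | 0.85 | 0.922 | 0.651 | 97.7% | 86.3% |
| 0.9 | 0.95 | 0.975 | 0.616 | 96.3% | 82.3% |

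**Step 3. Unequal SDs.** Let the 6-month SD be 1 and the baseline SD be k. The change-score variance is 1 + k² − 2rk. It exceeds the ANCOVA residual variance, 1 − r², by (k − r)². That is never negative, so apart from a few degrees of freedom ANCOVA does not lose. The gain shrinks as k approaches r:

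- k = 0.8, r = 0.5: 0.75 / 0.84 = 0.89, a saving of 11% rather than 25%.
- k = 0.7, r = 0.7: 0.51 / 0.51 = 1, no saving.

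**Step 4. Error rate under the null.** Simulation used 75 per arm and 10,000 runs at each of r = 0.3, 0.5 and 0.7.

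- Each test on its own: 4.7% to 5.0%.
- Adjusting only when the baseline difference has p < 0.05: 3.8%, 4.3% and 4.7%.
- Reporting whichever of the two tests is significant: 7.8%, 7.1% and 6.8%.

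**The case against.** The strongest reply is that nothing here is an error. The t-test is valid, the power statement is right, and the article already names ANCOVA, lists baseline and site among the covariates, and promises adjusted estimates. A condensed article may leave the exact model to a full protocol or analysis plan that is not shown. Much of this stands: the issue is efficiency and prespecification, not validity. But the article is not silent. It publishes a t-test, a bivariate examination and a covariate list that includes compliance. An analysis plan with a fixed model would have to depart from that text.

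Three stronger readings are tempting and are not supported.

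- *The primary test itself depends on the data.* An unadjusted t-test on a fixed outcome at a fixed time involves no covariate choice. Only the adjusted estimate and the choice between the two are open. The 6.8% to 7.8% error rate arises only if the significant result is picked, which the article does not propose. Adjusting on a significant baseline imbalance did not inflate the error rate.
- *The interaction test can withhold the 6-month result.* The article does say that "significant group-time interactions will allow for presentation of results by condition for each time point". However, the same sentence first provides estimates by condition and time without any such condition, and the mixed model is an optional analysis of trajectories. The 6-month comparison is fixed separately.
- *Ignoring site makes the intervals too wide by a known amount.* The article gives no share of variance due to site, and stable level differences between sites cancel in a change score. Any gain from site is unknown.

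**Conclusion.** The point holds as one of avoidable imprecision and an unsettled leading estimate. That the unadjusted test leads is read from Power analysis together with Statistical plan and data analysis; the article does not say so outright.

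Under equal SDs, the variance given up is (1 − r)/2: 35%, 25%, 15% and 5% at assumed r of 0.3, 0.5, 0.7 and 0.9. It matters most at the planned 40% attrition, where the t-test has little power in reserve. At 75 per arm, power is above 95% either way, and the benefit is mainly a narrower confidence interval. If r is near 0.9, or the SD ratio is near r, the gain is small.

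A reader should not infer that the trial is underpowered on its own inputs or that its primary test is invalid. Listing compliance as a covariate is a separate weakness of the same paragraph and does not depend on r.

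**What to change.** For CAIT, SEBT posteromedial reach and FAAM Sport:

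- Make the primary analysis a prespecified linear model of the 6-month value on group, baseline value and site, and name its group contrast, with 95% confidence interval, as the leading estimate.
- Delete the bivariate screening of covariates for these comparisons.
- Remove compliance from the covariates of the intention-to-treat comparison. The optional analysis limited to patients with at least 75% of the intervention can stay as a separate analysis.
- Keep the unadjusted change-score t-test as supportive.

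The cost is analysis wording only. Sample size, visits and data collection do not change, and the power statement can stay as a conservative figure.

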### Interventions

Patients in both the FIRE and SOC groups will complete two supervised and three unsupervised sessions during each week of the 6-week intervention, for a total of 12 supervised rehabilitation sessions and 18 unsupervised rehabilitation sessions. During the supervised sessions, patients will work directly with a credentialed rehabilitation specialist (physical therapist or athletic trainer) who was trained on the intervention procedures and demonstrated proficiency during prerecruitment calibration. The treating clinicians will schedule rehabilitation sessions with patients and record the date, duration of session, and exercises completed during each supervised session. Additionally, the treating clinician will record any reports of patient soreness, discomfort, or other symptoms and adjust the intervention consistent with the tenets of evidence-based practice. Patients will be instructed on how to complete the unsupervised exercises after the initial supervised session and will demonstrate the home exercises to the treating clinician before leaving the clinic to help ensure full understanding. To track compliance with unsupervised sessions, patients will be provided an exercise program and log to record the number of sessions, sets, and repetitions of exercises completed. Patients will be asked to demonstrate the exercises performed at home to assess recall and technique during each subsequent supervised session. Patients with reported non-compliance, limited recall, or reported displeasure with performance of the assigned exercises will be retrained and encouraged to continue with the allocated interventions. The treatment course will be modified (and annotated) as required based on the needs of the patient, treatment response, and patient preference. The home and supervised exercise library for both the SOC and FIRE programs have been included as supplements.

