### Foot intensive rehabilitation program

Details of the FIRE intervention can be found in the Additional file 1 (FIRE Supervised and Home Exercise Intervention Protocol). The FIRE intervention will include the progressive balance training, ankle and hip strengthening, and range of motion exercises from the SOC intervention; however, several exercises will be modified and added that concentrate on foot muscle activation, plantar cutaneous somatosensory feedback, and the integration of foot stability during movement. Plantar massage will consist of two, 1-min plantar massages with a 1-min rest between sets. This massage will be a combination of effleurage and petrissage techniques to the entire plantar aspect of the foot with the patient supine [28]. Four previously established exercises will target the IFMs including the short-foot, toe-spread-out, hallux extension, and lesser-toe extension [31, 32, 47]. In the first treatment session, patients will start each exercise in a seated position. Progression to double-limb stance and single-limb stance will occur when an exercise is done correctly for an entire session without compensation. A series of exercises will also target the extrinsic foot muscles involved in foot posture including resistive band supination and pronation, step ups with active supination or pronation and bilateral heel raises with a ball squeeze between the heels [48, 49]. The balance training exercises described for the SOC intervention will be completed during the FIRE intervention; however, the FIRE group will be instructed by the supervising interventionist to emphasize IFM activation during static balance exercises and after landing during dynamic balance exercises. The unsupervised sessions for the FIRE intervention will consist of single-limb balance, triceps surae stretching, supination and pronation resistance band, and intrinsic foot muscle exercises. Additionally, plantar massage will be self-administered by rolling the plantar surface of the foot on a textured massage ball on the ground [50].

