The primary analysis will be intent-to-treat (ITT), comparing groups as randomized. The ITT analysis will be performed using all randomized patients, where data for those terminated or lost to follow-up may be imputed using multiple imputation. If such methods are deployed, sensitivity analyses will be performed. Additional analysis will also be conducted comparing groups as they were randomized with data as observed. An attrition analysis will be conducted by comparing the demographics and outcomes measured at baseline in patients who completed follow-up to those who did not. Mechanisms for missing data will be investigated by comparing important covariates between patients with and without missing data at each time point. Furthermore, data on compliance measures will be captured within the weekly intervention logs, and a modified ITT may also be conducted but limited to those who achieved at least 75% of the intervention protocol across all six weeks. Ultimately, sensitivity analyses will be conducted comparing the results of our imputation methods to complete-case and available-data analyses. Throughout all ITT and as treated analyses, assumptions will be checked, and remedial measures will be deployed as needed.

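### Session compliance, recorded after randomisation, is listed as a potential adjustment covariate; if it differs by arm, the adjusted FIRE-SOC estimate could be biased in either direction

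*Protocol article*

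**What the plan says.** All of the analysis text is in the protocol article, section 'Statistical plan and data analysis'.

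- **Adjustment.** The plan is that "potential covariates will be examined with bivariate analyses, and comparisons requiring covariate adjustment will use regression modeling (e.g. ANCOVA, logistic regression". The candidates are baseline outcome values, demographic variables, prognostic indicators "and intervention compliance (% sessions completed".
- **Reporting.** "unadjusted and adjusted estimates will be presented with 95% confidence intervals". No sentence confines adjustment to secondary analyses.
- **Primary analysis.** "The primary analysis will be intent-to-treat (ITT), comparing groups as randomized".
- **Source of the compliance data.** "data on compliance measures will be captured within the weekly intervention logs".
- **Optional restricted set.** "a modified ITT may also be conducted but limited to those who achieved at least 75% of the intervention protocol across all six weeks".

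On the programmes themselves, 'Interventions' gives both arms the same schedule, "for a total of 12 supervised rehabilitation sessions and 18 unsupervised rehabilitation sessions". 'Foot intensive rehabilitation program' says that in FIRE "several exercises will be modified and added that concentrate on foot muscle activation", among other things.

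**The concern.** Every other type of covariate on the list describes the patient at entry. Compliance is different: it is a response to the programme the patient was assigned. Adjusting a randomised comparison for it conditions on something that assignment may have changed. The coefficient for group then compares FIRE and SOC patients with equal compliance, who need not be alike in motivation, early response or prognosis.

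The screening rule adds to the risk. The article does not say what the candidates are screened against. If it is outcome or arm, an association is exactly what would bring compliance into the model, and both associations together are what produce the bias.

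At stake is the adjusted estimate, which is to be shown with its confidence interval beside the unadjusted one. The plan labels effect sizes of 0.40 to 0.69 moderate and 0.70 or more strong, so an upward error of 0.10 would relabel a true 0.60.

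**Working it through.** **1. The plan's own figures.** 'Power analysis' gives an effect size of 0.6, two-sided 0.05 and 75 per group, with at least 95% power, and 80% at 40% attrition. The noncentral t distribution gives 95.5% at 75 per group. With attrition, 150 × (1 − 0.40) = 90, or 45 per group, which gives 80.4%. Both figures reproduce and are not in dispute. They rest on an unadjusted two-sample t-test, so removing a covariate does not change them.

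**2. Timing.** Compliance comes from logs kept over the six intervention weeks. It therefore cannot be known at randomisation.

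**3. Size of the shift (assumed inputs).** The article gives no compliance data, so these inputs are illustrative. Outcome and compliance are each scaled to a within-arm SD of 1. Let Δ be the as-randomised effect, s the mean compliance in FIRE minus that in SOC, and r the within-arm correlation of compliance with outcome. In a linear model:

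adjusted effect = Δ − r × s

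With Δ = 0.60:

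| s | r = 0.2 | r = 0.4 |
|---|---|---|
| −0.50 | 0.60 + 0.10 = 0.70 | 0.60 + 0.20 = 0.80 |
| −0.25 | 0.60 + 0.05 = 0.65 | 0.60 + 0.10 = 0.70 |
| 0 | 0.60 | 0.60 |
| +0.25 | 0.60 − 0.05 = 0.55 | 0.60 − 0.10 = 0.50 |
| +0.50 | 0.60 − 0.10 = 0.50 | 0.60 − 0.20 = 0.40 |

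A simulation of 4,000 trials with 75 per arm agreed at the two ends of the lower-compliance half: 0.650 and 0.800. The higher-compliance half follows from the same formula.

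**4. A second model.** Here a latent prognostic factor drives compliance (coefficient 0.5) and outcome (0.3), and compliance acts on outcome directly with coefficient 0 or 0.3. The within-arm slope is 0.5 × 0.3 = 0.15, or 0.15 + 0.3 = 0.45. Only lower FIRE compliance was simulated. With a true effect of zero:

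| s | Expected error of adjusted estimate | Simulated error | Type I error, adjusted test, 75 per group |
|---|---|---|---|
| 0 | 0 | about 0.00 | about 5% |
| −0.25 | 0.25 × 0.15 = 0.04 to 0.25 × 0.45 = 0.11 | 0.03 to 0.11 | 6% to 13% |
| −0.50 | 0.50 × 0.15 = 0.08 to 0.50 × 0.45 = 0.23 | 0.08 to 0.23 | 8% to 33% |

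The unadjusted estimate stayed at about 0.00 throughout.

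**5. The 75% set.** In the second model the cut-off was placed so that 80% of SOC passed, which is another assumption. About 72% of FIRE then passed at s = −0.25 and 63% at s = −0.50. The compliers-only estimate was off by 0.01 to 0.05 and by 0.04 to 0.11 respectively, less than the compliance-adjusted one. With s = 0 it was not biased.

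**The case against.** The strongest reply has four parts.

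*Compliance may not differ by arm.* The covariate counts sessions, and both arms have 12 supervised and 18 unsupervised. FIRE modifies SOC content as well as adding to it, and no session durations are given, so a heavier burden is plausible but not shown. This stands. The bias is conditional, and neither analysis was biased when arm did not shift compliance.

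*The primary result is largely protected.* The power calculation uses an unadjusted t-test, the primary analyses are described as comparisons of group means, and the primary analysis is by intention to treat. Compliance is only a potential covariate, and unadjusted estimates will be shown as well. This also stands. A reader might infer that the plan contradicts its own intention-to-treat principle or that its main result is biased. The text does not support that, because only an adjusted estimate that actually includes compliance is exposed.

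*The final covariate set may be left to a SAP that is not shown.* That would excuse an unfinished list. It does not excuse a list that names a post-randomisation variable as eligible.

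*The 75% analysis is optional, additional and defined where it is named.* Agreed. It cannot bias the primary comparison, and its fault is mainly the label.

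**Conclusion.** The point holds in a limited form. Listing compliance as an adjustment covariate for the randomised comparison is a wrong choice that the article itself states. It puts the adjusted estimate at risk. It does not affect the unadjusted intention-to-treat estimate.

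Under the assumed inputs, a true 0.60 SD could appear as anything from about 0.40 to 0.80 SD, an error of up to 0.20/0.60 = 33% either way, and zero if arm does not shift compliance. These figures illustrate the mechanism and do not forecast this trial.

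A reader might infer that the benefit of FIRE would be overstated. That requires compliance to be lower in FIRE and positively related to better outcome. The documents give neither, and higher compliance in FIRE would understate the effect.

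The 75% set is a secondary matter. It selects on behaviour after randomisation, so it is a per-protocol analysis, and 75% of two programmes with different content is not the same exposure.

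**What to change.** 1. Delete intervention compliance from the list of potential covariates, and state that adjustment of the FIRE-SOC comparison uses only variables measured before randomisation. Keep compliance for description by arm.
2. Rename the 75% analysis per-protocol and exploratory.
3. No complier-average analysis is needed. If one is wanted, present it as exploratory and state its exclusion restriction. That assumption is doubtful here: both arms are active and FIRE contains SOC components, so a patient who does not comply with FIRE also misses SOC content that the same patient might have received under SOC.

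Items 1 and 2 change wording only. Data collection is unchanged, and planned power stays at about 95.5% with 75 per group and 80.4% with 45.
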